## Abstract

**Background:**

The increasing prevalence of dementia in the next decades is accompanied by various societal and economic problems. Previous studies have suggested that physical activity positively affects motor and cognitive skills in individuals with dementia (IWD). However, there is insufficient evidence probably related to several methodological limitations. Moreover, to date adequate physical activity interventions specifically developed for IWD are lacking.

**Objective:**

This study aims to investigate the effectiveness of a multimodal exercise program (MEP) on motor and cognitive skills in IWD in a high-quality multicenter trial.

**Methods:**

A multicenter randomized controlled trial with baseline and postassessments will be performed. It is planned to enroll 405 participants with dementia of mild to moderate stage, aged 65 years and older. The intervention group will participate in a 16-week ritualized MEP especially developed for IWD. The effectiveness of the MEP on the primary outcomes balance, mobility, and gait will be examined using a comprehensive test battery. Secondary outcomes are strength and function of lower limbs, activities of daily living, and cognition (overall cognition, language, processing speed, learning and memory, and visual spatial cognition).

**Results:**

Enrollment for the study started in May 2015. It is planned to complete postassessments by the beginning of 2017. Results are expected to be available in the first half of 2017.

**Conclusions:**

This study will contribute to enhancing evidence for the effects of physical activity on motor and cognitive skills in IWD. Compared to previous studies, this study is characterized by a dementia-specific intervention based on scientific knowledge, a combination of motor and cognitive tasks in the intervention, and high standards regarding methodology. Findings are highly relevant to influence the multiple motor and cognitive impairments of IWD who are often participating in limited physical activity.

**Trial Registration:**

German Clinical Trials Register DRKS00010538; https://drks-neu.uniklinik-freiburg.de/drks_web/navigate.do?navigationId=trial.HTML&TRIAL_ID=DRKS00010538 (Archived by WebCite at http://www.webcitation.org/6oVGMbbMD)

## Introduction

Dementia is one of the most frequently occurring diseases in the elderly [1], and the World Health Organization has declared dementia a public health priority [2]. The current prevalence of dementia is estimated at 47 million worldwide [3] and will presumably increase because of expected demographic changes [4]. This increasing prevalence (expected 135 million in 2050 [5]) will be accompanied by several societal and economic problems including rising disease-related costs and increasing demands for caregiving [2].

Dementia is a syndrome which comprises several different types of usually chronic and progressive diseases of the brain (eg, Alzheimer disease or vascular dementia) [6]. It encompasses diverse impairments and symptoms which affect individuals with dementia (IWD) in different ways depending on dementia type [7]. According to the *International Statistical Classification of Diseases and Related Health Problems, Tenth Edition* (ICD-10) [6], a diagnosis of dementia minimally requires the following symptoms: an impaired memory, further cognitive disturbances, and noncognitive disorders such as disturbed emotional control. These impairments potentially influence activities of daily living (ADL) [6] accompanied by an increasing loss of independence to a greater or lesser extent [8]. In addition, IWD suffer from motor and functional impairments such as affected gait and balance performance as well as transfer movements, which are not only reported in advanced stages [9-11].

To date, there is no cure for dementia, and commonly used medications for treating the symptoms of dementia have side effects emphasizing the urgent need for nonpharmacological interventions [12]. For instance, there is evidence that physical activity positively affects motor and cognitive skills of cognitively healthy elderly people [13]. Moreover, the number of studies analyzing this issue in IWD has increased [14-18]. For this sample, there are also systematic reviews and meta-analyses examining the effects of physical activity on balance, mobility, and gait as well as strength and ADL. Regarding balance, 3 of 5 reviews reported no or no clear benefit of physical activity [19-21] with largely varying effect sizes from small negative to large positive values [22,23]. Even if a positive effect of physical activity on mobility can be reported [19,21,24], the overall conclusion is inconsistent [20] with effect sizes ranging from small negative to large positive values [22,23]. Only a few reviews have considered specific aspects of gait function. One review has shown no to medium effect sizes for normal gait speed [22]. Reviews focusing on strength of lower limbs and ADL mainly reported improvements [19-26]. However, the small number of high-quality studies and the large heterogeneity in methods used in these studies represent insufficient evidence regarding the effects of physical activity [22,26].

Reviews and meta-analyses examining the effects of physical activity on cognitive skills in IWD mainly assess overall cognition. Of 6 reviews and meta-analyses, 3 found no evidence for the benefit of physical activity on cognition in IWD [20,26,27] while the others found a positive overall effect [12,19,28]. Groot et al [12] stated that overall effects of physical activity on cognition are comparable to the effect size observed in meta-analyses examining the effectiveness of pharmacotherapy in IWD [29-31].

Most of the systematic reviews and meta-analyses suggest even if evidence is lacking that physical activity positively affects IWD, for example, in balance, mobility, and cognition. Their conclusions are that there is an urgent need for high-quality intervention studies [12,20,22,23,27]. In their opinion, methodological shortcomings including insufficient reporting of methods and results and small samples as well as the use of inadequate outcome measures [12,22,27,28] could be responsible for the lack of conclusive evidence. Furthermore, Hauer et al [32] discussed that low effectiveness of existing physical activity interventions may explain negative or inconsistent findings in previous studies. It can be speculated that the effectiveness of existing training interventions is limited by inappropriate intensity, duration, type of training, lack of specific interventions, or individualization of training [32].

This study will investigate the effects of a physical activity intervention on motor and cognitive skills. The intervention focuses on dementia-specific motor deficits and aims to influence the underlying motor performance, which depends on complex cognitive processes like integrating sensory information, central processing, or efferent motor output [33]. This reflects the close connection between cognitive and motor functions and could provide insights in disease progression [34]. It is highly relevant for IWD to counteract and possibly reduce dementia-related motor deficits which typically result in distinct constraints of mobility-dependent quality of life as well as loss of independence and higher risk for falls [35-37]. Hence, primary outcomes are based on 3 considerations: dementia-specific motor deficits, relevance for everyday life, and measurement quality (direct and feasible measurements). Balance, gait, and mobility fulfill all requirements and influence quality of life [9,10,38,39]. ADL are defined as secondary outcomes because they are considered an entire construct related to several motor and cognitive skills. Thus, measuring ADL is more difficult and less objective than measuring balance, mobility, and gait. Further, we chose strength and function of lower limbs and cognition as secondary outcomes because of their expected influence on primary outcomes.

Aiming to overcome the above mentioned methodological limitations, we will realize a high-quality multicenter trial with a sustainable intervention close to everyday life. The following aims will be addressed.

Primary aim: to determine the effect of a multimodal exercise program (MEP) compared to conventional treatment (eg, medication, care, therapeutic applications) on balance, mobility, and gait. We hypothesize that a 16-week MEP in addition to conventional treatment affects balance, mobility, and gait in IWD more than the conventional treatment. Additionally, we will compare different subgroups (eg, according to sex, stage of dementia, or attendance).

Secondary aim: to investigate the influence of mediator and moderator variables on primary outcome measures. We assume that the effects of physical activity on balance, mobility, and gait are caused or influenced by changes in underlying motor and cognitive skills.

Comparably, we will investigate the effect of MEP on the secondary outcomes strength and function of lower limbs, ADL, and cognition as well as the effect of mediator and moderator variables on ADL. By addressing these aims, this study contributes to enhancing evidence concerning the effects of physical activity on motor and cognitive skills in IWD.

## Methods

### Study Design

The study design has been primarily defined to address the primary aim of the study on the effectiveness of a 16-week MEP. For this reason, we will perform a multicenter randomized controlled trial with baseline and postassessments and an allocation ratio of 2:1 for intervention (IG) and control group (CG), respectively. Ethical approval has been obtained from the ethics commission of the Karlsruhe Institute of Technology. The study is retrospectively registered in the German National Register of Clinical Trials [DRKS00010538]. This study protocol considers guidelines and recommendations of the Standard Protocol Items: Recommendations for Interventional Trials (SPIRIT) [40,41] and Consolidated Standards of Reporting Trials (CONSORT) statements [42-44].

### Participants

Participants for this study will be recruited in public, private, and charitable care facilities in southwestern Germany, in particular in the metropolitan region Rhein-Neckar and the district around Karlsruhe. All randomly selected care facilities offer inpatient care for approximately 60 to 300 residents and provide a common room where the intervention will be performed. A total of 3 recruitment periods with consecutive sampling within each care facility are planned.

Employees of care facilities will identify possible participants with the purpose to fulfill selection criteria.

Inclusion criteria include (1) diagnosis of dementia or suspected dementia (based on the assessment of the objective ICD-10 criteria by employees and the examination of cognitive abilities with Mini-Mental State Examination [MMSE][45]), (2) Alzheimer disease, vascular dementia, or other primary dementia (all types caused by neurodegenerative or vascular diseases: eg, lewy body dementia or frontotemporal dementia [46]), (3) mild to moderate stage of dementia (MMSE 10-24), (4) age above 65 years, (5) walking ability of approximately 10 meters with or without walking aid, and (6) clearance by general practitioner.

Exclusion criteria include (1) secondary dementia (all types resulting from organic illness or injury: eg, toxic substances or brain injuries [46]), (2) other severe cognitive impairments, (3) other severe neurological disease, (4) other severely acute diseases, and (5) severe motor impairments.

Potential participants will receive a comprehensive information letter and an informed consent form, which will be signed by individuals or their legal guardians prior to the study. The informed consent along with clearance of participant’s general practitioner allow scheduling of baseline assessments where eligibility will be verified according to the inclusion and exclusion criteria. Flow of participants is illustrated in Figure 1.

**Figure 1 figure1:**
[figure not shown]
Flow of participants.

### Intervention

The intervention is specifically developed for this study based on theoretical considerations, results of a pilot study [47], and a literature review [48]. The combination of motor and cognitive tasks used in the MEP aims to enhance the effectiveness of physical activity on cognition. This is theoretically supported by findings in healthy older adults showing that the combination of both yields larger effects on cognition than using each alone [49]. The pilot study (n=19) aimed to prove feasibility of the intervention and allowed first insights regarding the effectiveness. After a 10-week intervention, IG showed no significant changes in Alzheimer Disease Assessment Scale–Cognitive Subscale (ADAS-Cog, German version) [50] sum score but significant improvements in subscore orientation/praxis. In contrast, we found a significant decline in ADAS-Cog sum score of CG [47]. Moreover, IG showed significant improvements in get-up-and-go test whereas CG did not significantly improve (unpublished results). The literature review aimed at giving recommendations for designing interventions for IWD. Analyzed studies showed that a physical activity intervention for IWD should at least last 4 months with 2 to 3 sessions of 45 to 60 minutes per week. Moreover, interventions focusing on several motor skills (eg, endurance, strength, balance) seemed to be more effective than interventions with only 1 task [48]. Hence, the 10-week intervention of the pilot study has been revised for the current study. The revision, which aimed to provide a balanced MEP with specific, adequate, and intensity-demanding tasks, comprises adjustments of contents (motor qualities as well as connection between motor and cognitive tasks) and intervention duration (extension to 16 weeks).

The MEP will be guided by 2 skilled instructors with experience in sports science and performed as group training mainly in a seated position. A group will consist of a maximum of 12 participants and will be joined by familiar caregivers to support the instructors if needed. The underlying didactic concept focuses on specific needs and characteristics of IWD and includes increased supervision realized by 2 instructors, adaptation to the cognitive level of participants, adjusted communication (eg, simple language, nonverbal aspects), ritualization to give orientation and familiarity, and adequate complexity by simple and well-structured cognitive and motor tasks.

To ensure high standards and comparability, each session is planned in detail and all instructors participate in a special training focusing on structure and contents of MEP as well as special demands resulting from the characteristics of IWD. A detailed training manual is provided for instructors, and the adherence to this manual will be emphasized. To ensure standardization, all tasks are described precisely and photographs are provided.

Providing a sense of security is an important aspect realized by ritualization. To satisfy this ritualization, the general sequence is identical for all sessions including an imagination of experienced journeys. Each session is divided into 3 parts: arrival, destination, and departure. Whereas arrival and departure remain consistent over the whole intervention period, a new travel destination is selected every time. A total sample session of MEP is found in Multimedia Appendix 1.

The arrival as beginning ritual of each training session takes about 5 to 7 minutes and aims to prepare participants for the following main part. Tasks for mobilization and stimulation of the cardiovascular system are linked to cognitive activation.

The main part of MEP is the destination (about 35 minutes) which includes tasks for strength (43%), balance (25%), endurance (16%), flexibility (13%), and not further specified tasks (3%) (see Figure 2). In addition, cognitive tasks are incorporated to stimulate memory, attention, language, and executive functions. Tasks are carried out with medium to submaximal intensity. Throughout the intervention, there will be a progression concerning intensity as well as motor and cognitive requirements. Examples of different motor and cognitive tasks as well as examples for their progression are given in Table 1.

**Table 1 table1:** Examples of motor and cognitive tasks of the multimodal exercise program and their progression.

		Simple performance	Progressive performance developed within the 16 weeks

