### Sample Size

The required sample size was calculated via G*Power version 3.1.9.2 (Heinrich Heine University of Dusseldorf) [73], taking into account the following parameters: analysis of variance (ANOVA) for repeated measures, within-between interaction, small effect size (ɳ²=0.01, d=0.2) [74], 2-sided α-error of .05, power of .80 (1-β), and 2 groups and 2 measurements. The small effect size used for the calculation of required sample size is based on literature review and assumptions of relevant changes for IWD. Previous studies have reported high variation in the effect sizes of the primary outcomes balance, mobility, and gait. In their review, Blankevoort et al [22] reported small negative to large positive effect sizes for balance (d=–0.24 to d=3.59) and functional mobility (d=–0.25 to d=2.37) as well as no to medium effect sizes for normal gait speed (d=–0.11 to d=0.50). These reported variations do not allow determining actual effect sizes. Thus, the magnitude of relevant changes has to be considered to further support the selection of a small effect size. Because dementia is characterized by rapid progression linked to multiple impairments, it is assumed that even small effects are relevant. The calculation of sample size results in a required sample size of 100 participants for each group (total sample size of 200 participants). Considering reasons for dropout, the sample is set to 405 participants.

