### Allocation

Group allocation to IG and CG will be performed by minimization to obtain randomized groups with minimum group differences. Subjects rather than care facilities will be randomized to avoid confounding effects of the geographic location, and minimization will be done separately for each care facility based on the baseline criteria MMSE, sex, age, and baseline performance of modified 30-second chair-stand test. Minimization will be performed with the program MinimPy version 0.3 [75], which includes a random element. The first participant is allocated randomly to IG or CG. Subsequent participants are allocated to each group correspondingly to achieve the least imbalance between groups. Including a random element, participants will be allocated to the better fitting group with a probability of 70%. An allocation ratio of 2:1 is selected because of above-mentioned assumptions regarding dropouts. The input order of participants for allocation will be randomly defined by an assigned number for each participant given prior to minimization.

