### Statistical Analysis

All statistical analysis will be done with SPSS version 23 (IBM Corp). Trained and experienced investigators will evaluate and enter data. Investigators evaluating and entering data are not the same as investigators assessing outcomes. The number of investigators is limited to 2 per assessment method. Prior to actual analysis, interrater reliability (Cohen kappa [76], intraclass correlation coefficient [77]) will be calculated and plausibility (eg, considering range and distribution) will be checked to minimize errors caused by data evaluation and entry.

Because of expected large dropout rate, which can lead to a critical amount of missing data, 2 separate analysis sets are planned: an intention-to-treat analysis and a per-protocol analysis. In the intention-to-treat analysis, all randomized participants regardless of protocol adherence will be included and missing data will be substituted by multiple imputation. Participants with sufficient attendance and adherence to the intervention as well as complete assessments of primary outcomes will be included in the per-protocol analysis, where missing data will not be considered.

Baseline values of participant characteristics will be compared between IG and CG using chi-square tests for categorical data, Mann-Whitney-U tests for nonparametric variables, and *t* tests for continuous and normally distributed parameters. For all normally distributed data (checked by Shapiro-Wilk test), mean and standard deviation will be calculated, and medians and interpercentile ranges will be calculated for not normally distributed data. Treatment effects will be analyzed using 2-factor ANOVA with repeated measurement. A 2-sided *P* value less or equal to .05 will be considered to indicate statistical significance. In addition, 95% confidence intervals and partial Eta² will be calculated. Changes in motor and cognitive function are possible mediators and moderators. These mediating and moderating effects on primary outcomes will be analyzed using multiple linear regression models. Additional explorative data analysis exceeding the proposed planned analyses will be performed. Depending on data structure, adequate analysis methods will be defined. These analyses aim to consider further influencing factors or subgroup analysis as well as the development of forecast models.

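### The treatment-effect ANOVA has no training-group or facility term, so its standard errors are not valid: too small where 16-week change correlates within training groups, partly offset where facilities differ in change

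*Protocol article*

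**What the plan says.** All references are to the Methods of the protocol article.

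- **Intervention.** The programme is "performed as group training mainly in a seated position", led by 2 instructors. On size and support: "A group will consist of a maximum of 12 participants and will be joined by familiar caregivers". The control arm continues conventional treatment and has no such groups.
- **Allocation.** The unit is the individual: "Subjects rather than care facilities will be randomized to avoid confounding effects of the geographic location". Facility still shapes the procedure, because the minimisation runs within each one, using MMSE, sex, age and chair-stand performance, at a 2:1 ratio. Each facility therefore contributes to both arms.
- **Statistical Analysis.** "Treatment effects will be analyzed using 2-factor ANOVA with repeated measurement". No training-group, instructor or facility term, mixed model or robust standard error is named for this test. The later sentence that leaves methods to the structure of the data concerns additional exploratory analyses only.
- **Sample Size.** The inputs are a "small effect size (ɳ²=0.01, d=0.2") and "2-sided α-error of .05, power of .80 (1-β), and 2 groups and 2 measurements". The result is a "required sample size of 100 participants for each group (total sample size of 200 participants"). No ICC or design effect enters.

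**The concern.** With 405 enrolled at 2:1, 270 people are in the intervention arm. In groups of at most 12 that is at least 23 training groups (270/12 = 22.5). Members of a group share instructors, supporting caregivers, group dynamics and local adaptations for 16 weeks. These influences arise after randomisation and in one arm only, so randomising individuals does not remove them. If they make members' changes resemble each other, the intervention mean is less precise than the ANOVA assumes.

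Facility also matters, in the opposite direction. Both arms are present in every facility, so an influence on change that all residents of a facility share cancels from the treatment contrast. An ANOVA that omits facility leaves this variance in its error term, which makes the standard error too large.

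At stake are the true level of the 5% tests and the coverage of the 95% confidence intervals.

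**Working it through.** **1. The plan's own figure.** For the within-between interaction, λ = f²·N·m/(1−ρ), with f = 0.10 (η² = 0.01) and m = 2 measurements. The correlation ρ is not stated; ρ = 0.5 is assumed because it returns the stated number. At N = 200, λ = 0.01 × 200 × 2 / 0.5 = 8, and power is 0.804. The stated 200 is thus reproduced with all participants treated as independent. Setting λ = d²·N/4 gives a standardised difference on the change score of d = √(4 × 8/200) = 0.40.

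**2. Clustering in the intervention arm only, no facility effect.** DE = 1 + (m−1)·ICC, with m now the group size. The ratio of true to naive variance is (DE/n₁ + 1/n₀)/(1/n₁ + 1/n₀), which at 2:1 reduces to (DE + 2)/3. The actual two-sided error is 2·[1 − Φ(1.96/r)], where r is the ratio of standard errors. The ICC range is an assumption. Group sizes are 12 (the stated maximum) and 7.8 (12 less the plan's 35% loss).

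| Group size | ICC | DE | r (true/naive SE) | Type I error |
|---|---|---|---|---|
| 12 | 0.01 | 1.11 | 1.018 | 5.4% |
| 12 | 0.02 | 1.22 | 1.036 | 5.9% |
| 12 | 0.05 | 1.55 | 1.088 | 7.2% |
| 12 | 0.10 | 2.10 | 1.17 | 9.4% |
| 7.8 | 0.01 | 1.07 | 1.011 | 5.3% |
| 7.8 | 0.02 | 1.14 | 1.022 | 5.5% |
| 7.8 | 0.05 | 1.34 | 1.055 | 6.3% |
| 7.8 | 0.10 | 1.68 | 1.108 | 7.7% |

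The true standard error is 2% to 17% larger for groups of 12. Put the other way, the naive one is understated by 1 − 1/r, about 2% to 15%. For 7.8 per group the true standard error is 1% to 11% larger. A simulation of the naive test on change scores (22 facilities, 12 intervention and 6 control participants each, no facility effect) gave 5.9%, 7.2% and 9.7% at ICC 0.02, 0.05 and 0.10.

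**3. Adding a facility effect on change.** Let v_f and v_g be the facility and training-group shares of the variance, with 12 and 6 participants per facility and one group in each. Per facility, the true variance of the contrast is v_g + (1−v_f−v_g)/12 + (1−v_f)/6. The naive variance is about 1/12 + 1/6 = 0.25. The ratio is therefore about 1 − v_f + 3.67·v_g, so the naive standard error is too small on net only if v_g exceeds about 0.27·v_f.

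| v_f | v_g | Variance ratio | Type I error, formula | Type I error, simulated |
|---|---|---|---|---|
| 0.05 | 0.02 | 1.023 | 5.3% | about 5.5% |
| 0.05 | 0.05 | 1.133 | 6.6% | about 6.7% |
| 0.10 | 0.02 | 0.973 | 4.7% | about 4.8% |

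A separate simulation run gave 5.3%, 6.3% and 4.9%, the same picture within simulation error.

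**4. Power.** A 35% loss leaves about 175 and 88 (270 × 0.65 = 175.5; 135 × 0.65 = 87.75). With d = 0.40, power is Φ(0.40/SE − 1.96), SE = √(DE/175 + 1/88).

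- Independence: SE = 0.131, power about 87%.
- ICC 0.05, groups of 12 (DE 1.55): SE = 0.142, power 80%.
- ICC 0.05, 7.8 per group (DE 1.34): SE = 0.138, power 83%.
- ICC 0.10, the top of the assumed range (DE 2.10 and 1.68): SE = 0.153 and 0.145, power 74% and 79%.

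**The case against.** The strongest case against the point has five parts.

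- **Direction is not certain.** Allocation within facility means a shared facility effect on change makes the naive standard error too large. This stands: with v_f = 0.10 and v_g = 0.02 there is no inflation. It does not rescue the ANOVA, because two omitted variance components would have to cancel by chance. The offset is also limited in kind. The group-by-time test works on change, so stable differences in level between facilities cancel anyway; only facility differences in 16-week change count.
- **The upper figures stack worst cases.** Twelve is a maximum and no average is given. The 9.4% needs full groups, ICC 0.10 and no facility effect together. This stands, and at ICC 0.01 to 0.02 the effect is small.
- **Delivery is standardised.** The Intervention section describes a manual, instructor training and a fixed session sequence. These may lower the ICC. They cannot be shown to remove it, and the Challenges section accepts that some adaptation is unavoidable.
- **The detail may sit in a fuller plan.** That would answer an omission. Here the article names the test, and the named test does not match the delivery it describes.
- **Enrolment exceeds the calculated need.** The 405 planned against 200 required absorbs a moderate design effect on power. It does nothing for the type I error.

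A reader might infer that the 5% level is exceeded for every outcome, or that the trial is underpowered. The protocol article supports neither. No ICC is given for any outcome, and the ICC may differ between balance, walking times, gait parameters and cognition. Power meets the 80% target at ICC 0.05.

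**Conclusion.** The point holds in a conditional form. The planned ANOVA does not reflect one-arm group delivery or allocation within facility, so its standard errors are not valid. They are too small for outcomes whose change correlates within training groups, less so, and occasionally not at all, where facilities differ in change irrespective of arm.

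Under the assumed ICC range and no facility effect, the nominal 5% test runs between 5.3% (7.8 per group, ICC 0.01) and 9.4% (12 per group, ICC 0.10). With a facility ICC of 0.05 to 0.10 and a group ICC of 0.02 to 0.05 it runs at about 4.8% to 6.7%. All of this rests on ICCs and average group sizes that the protocol article does not give.

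Sample size is not the main issue. Power would fall below 80% with 175 and 88 analysed only towards the top of the assumed ICC range. That statement itself depends on the 0.40 change-score effect implied by ρ = 0.5. Label: cheap improvement.

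**What to change.** In Statistical Analysis, replace the 2-factor repeated-measures ANOVA for treatment effects with a partially nested mixed model:

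- a random training-group effect in the intervention arm, with control participants as singletons;
- facility as a fixed or random effect (where a facility has one training group, its controls allow the two to be separated);
- Satterthwaite degrees of freedom.

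Record a training-group identifier for each intervention participant. Instructors already document attendance at each session, so membership should be recoverable. Include facility and training group in the multiple imputation model for the intention-to-treat set; otherwise the imputed values dilute the clustering that the analysis model is meant to capture. Report the estimated ICC for each primary outcome.

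The cost is one data field and a little more analysis work. Confidence intervals may become somewhat wider, or narrower where facility effects dominate. Recruitment, allocation and delivery do not change.
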